## Abstract

**Background:**

A growing body of evidence suggests that SARS-COV-2 infection during pregnancy may affect maternal-fetal outcomes and possibly result in implications for the long-term development of SARS-CoV-2–exposed children.

**Objective:**

The PROUDEST (Pregnancy Outcomes and Child Development Effects of SARS-CoV-2 Infection Study) is a multicenter, prospective cohort study designed to elucidate the repercussions of COVID-19 for the global health of mothers and their children.

**Methods:**

The PROUDEST trial comprises 2 prospective, sequential substudies. The *PREGNANT* substudy will clinically assess the effects of SARS-CoV-2 infection on pregnancy, childbirth, and puerperium from a mechanistic standpoint to elucidate the pregnancy-related inflammatory and immunological phenomena underlying COVID-19. Pregnant women aged 18-40 years who have been exposed (proven with laboratory tests) to SARS-CoV-2 (group A; n=300) will be compared to control subjects with no laboratory evidence of in-pregnancy exposure to the virus (group B; n=300). Subjects exposed to other infections during pregnancy will be excluded. The *BORN* substudy is a long-term follow-up study that will assess the offspring of women who enrolled in the prior substudy. It will describe the effects of SARS-CoV-2 exposure during pregnancy on children’s growth, neurodevelopment, and metabolism from birth up to 5 years of age. It includes two comparison groups; group A (exposed; n=300) comprises children born from SARS-CoV-2–exposed pregnancies, and group B (controls; n=300) comprises children born from nonexposed mothers.

**Results:**

Recruitment began in July 2020, and as of January 2021, 260 pregnant women who were infected with SARS-CoV-2 during pregnancy and 160 newborns have been included in the study. Data analysis is scheduled to start after all data are collected.

**Conclusions:**

Upon completion of the study, we expect to have comprehensive data that will provide a better understanding of the effects of SARS-CoV-2 infection and related inflammatory and immunological processes on pregnancy, puerperium, and infancy. Our findings will inform clinical decisions regarding the care of SARS-CoV-2–exposed mothers and children and support the development of evidence-based public health policies.

**Trial Registration:**

Brazilian Register of Clinical Trials RBR65QXS2; https://ensaiosclinicos.gov.br/rg/RBR-65qxs2

**International Registered Report Identifier (IRRID):**

DERR1-10.2196/26477

## Introduction

### Background

The natural history of COVID-19, a disease caused by SARS-CoV-2, is still being written. Individuals infected with SARS-CoV-2 may present with a broad spectrum of clinical manifestations, from no symptoms to dramatically progressive disease symptoms that eventually result in death [1,2]. Some individuals develop intense inflammatory and procoagulant responses that can result in severe pulmonary damage, which is the main cause of COVID-19 morbidity and mortality.

The pathophysiological phenomena that take place in other human tissues that are potentially targeted by SARS-CoV-2 need further investigation. A central nervous system viral tropism has been postulated based on reports of neurological events such as stroke, acute hemorrhagic encephalopathy, seizures, and the loss of smell and taste [3,4].

To date, little is known about the effects of COVID-19 on women during pregnancy and puerperium [5,6] and its consequences for women’s offspring (from the neonatal period through the first years of life) [7-9]. Thus, there is still a lack of a robust evidence base for the proper management of these mothers and children.

Data from previous epidemics of viral-induced respiratory distress syndrome have shown that pregnant and puerperal women have a high risk of developing life-threatening clinical outcomes [10]. These generally worse outcomes have been attributed to physiological changes in the immune and cardiopulmonary systems that occur during pregnancy [11]. Examples of epidemics include the H1N1 influenza, SARS-CoV (severe acute respiratory syndrome coronavirus), and MERS-CoV (Middle East respiratory syndrome coronavirus) epidemics, during which pregnancy mortality rates reached 27% [10,12,13].

Despite the structural similarities between coronaviruses, the initial reports for pregnant women with COVID-19 showed lower rates of intensive care unit admission, orotracheal intubation, and death during the SARS-CoV-2 outbreak than those during the SARS-CoV and MERS-CoV outbreaks [9,13]. However, more recent papers have shown higher morbidity and mortality rates among pregnant women than those among nonpregnant women. Several aspects of embryo implantation [14], placental development [15], and delivery dynamics [16] seem to be impaired by the inflammatory response driven by immune cell subtypes at the maternal-fetal interface [17]. Such phenomena may precipitate preeclampsia, spontaneous abortion, intrauterine growth restriction, and premature birth [18-21].

Most of the available data on pregnant women exposed to SARS-CoV-2 were obtained during the second half of pregnancy. Thus, SARS-CoV-2 infection during all stages of pregnancy, including the early stages of gestation, has not been fully investigated. Nevertheless, as the disease spreads worldwide, more women are being exposed to the virus during early gestation and midgestation, and new data have been accruing [22].

Studies evaluating the vertical transmission of SARS-CoV-2 are still inconclusive [6,23-25]. Investigations of placentas from women infected with SARS-CoV-2 have suggested that there is a low likelihood of viral transplacental transmission. However, the potentially hazardous effects of inflammatory and prothrombotic environments on placental function and, consequently, fetal growth could not be ruled out [26-28].

To date, the few reports on postnatally infected neonates have shown that they exhibit either no symptoms or mild clinical forms of COVID-19 with favorable outcomes. However, the younger the infant is, the higher the risk of critical outcomes [22,29].

Maternal SARS-CoV-2 infection would potentially expose a fetus not only to direct viral effects but also to the placental inflammatory response and the maternal cytokine storm [5,7,22]. Such processes and their consequences have not been extensively studied. The understanding of these phenomena should contribute to the proper management of children born to mothers infected with SARS-CoV-2.

A case series on the clinical aspects of newborns of COVID-19–exposed mothers reported a low risk of adverse outcomes for late pregnancy exposure and stated that there is a paramount need for close follow-ups [30]. Other reports have presented data showing no adverse effects on neonates born to mothers who tested positive for COVID-19. Furthermore, Liu et al [31] described 19 completely asymptomatic neonates from Wuhan, China.

A few studies however have reported that SARS-CoV-2 test–negative neonates born to mothers who tested positive and developed critical illnesses might present ominous clinical profiles. This is suggestive of the potential impact of inflammatory processes on fetal physiology. Romagano et al [32] reported a prevalence rate of 6.9% for symptomatic pregnant women infected with SARS-CoV-2 among 1053 deliveries at a large hospital network in New Jersey, United States. They reported that 8 pregnant women were critically ill and 7 neonates tested negative (via reverse transcriptase–polymerase chain reaction [RT-PCR]); 1 neonate was not yet delivered at the time of testing. All neonates were preterm and appropriately sized for their gestational age except for one (small for their gestational age). They were all separated from their mothers after delivery, and all of them developed respiratory distress and required neonatal intensive care unit admission. Anemia and hyperbilirubinemia of prematurity, temperature instability, and feeding problems were reported in some of the neonates.

Several other studies have reported symptoms among SARS-CoV-2 test–negative neonates born to mothers with COVID-19, such as rashes [33], facial ulceration [33], the need for noninvasive oxygen support [33], transient lymphocytopenia [34], impaired liver function [34], disseminated intravascular coagulation, and even multiple organ failure leading to death [35]. There are many critical questions regarding the standards of care for SARS-CoV-2–exposed pregnant women and their offspring that have yet to be answered, and guidelines are still being developed around the world [8,36,37]. Therefore, the overall purpose of this study is to describe the effects of in-pregnancy SARS-CoV-2 infection and related inflammatory and immunological phenomena on the health of SARS-CoV-2–exposed women and their offspring.

### Objective

Our specific aims are (1) to study the effects of COVID-19 on maternal and obstetric morbidity and mortality, including those of indicators such as preeclampsia, abortion, fetal malformation, fetal growth, and premature birth; (2) to investigate the presence of SARS-CoV-2 and anti–SARS-CoV-2 antibodies in the cerebrospinal fluid (CSF) of women with symptomatic COVID-19 undergoing spinal anesthesia for a cesarean section; (3) to determine the serum proinflammatory and regulatory cytokine profiles of pregnant women with symptomatic COVID-19; (4) to determine the CSF proinflammatory and regulatory cytokine profiles of pregnant women with symptomatic COVID-19 undergoing spinal anesthesia for a cesarean section; (5) to study the histopathological markers of inflammatory and thrombotic phenomena in the placenta; (6) to study the correlations between the aforementioned serum and histologic biomarkers of COVID-19 and the outcomes of pregnancy, delivery, puerperium, and childbirth as well as the correlations between biomarkers and short- and long-term health outcomes during infancy; (7) to study the association between the use of maternal pharmacological therapy for treating COVID-19 and offsprings’ health outcomes; (8) to evaluate the effects of COVID-19 exposure during different stages of pregnancy on fetal, neonatal, and infantile morbidity and mortality; and (9) to evaluate the effects of in-pregnancy COVID-19 exposure on children’s somatic and neurological development and energy metabolism from birth up to 5 years of age.

## Methods

### Study Design

The PROUDEST (Pregnancy Outcomes and Child Development Effects of SARS-CoV-2 Infection Study) is a multicenter, longitudinal, prospective observational study that will be conducted in two sequential stages—the *PREGNANT* and *BORN* branches (or substudies). Each stage will have two parallel groups (exposed and nonexposed) for comparisons. The PROUDEST is designed to address the multifaceted questions surrounding the impact of COVID-19 exposure during pregnancy on the global health of mother-child dyads (Figure 1).

**Figure 1 figure1:**
[figure not shown]
Pregnancy Outcomes and Child Development Effects of SARS-CoV-2 Infection Study follow-up flowchart.

The PREGNANT substudy will follow—until day 21 postpartum—pregnant women who are exposed to SARS-CoV-2 at any phase of gestation and compare them to a control group consisting of nonexposed pregnant women. The BORN substudy will follow the children of the women included in the preceding (PREGNANT) branch. These children will be allocated into two comparison groups (exposed and nonexposed) according to their mothers’ in-pregnancy exposure status and will be followed up by a multidisciplinary team of health professionals from birth up to the age of 5 years. This team will conduct regular consultations every month up until the children reach 6 months of age, every 3 months up until the children reach 2 years of age, and every 6 months up until the children reach 5 years of age. Mothers and children may attend nonscheduled visits, as needed, for clinical reasons as well as specific appointments for conducting the procedures and tests described in this protocol.

The PROUDEST will be conducted from July 2020 to December 2026 in Brasília, Brazil. The recruitment of pregnant and newborn dyads will be carried out by using data from the Epidemiological Surveillance Center of the Federal District. These mother-fetus dyads will be followed up to childbirth (and puerperium in the case of mothers) until December 2021, which is when the last included dyads are expected to undergo childbirth in two different hospitals—the University Hospital of Brasília and Asa Norte Regional Hospital (the reference public medical center for COVID-19 in the Federal District in Brazil). Both hospitals are located in central urban areas and are included in the Brazilian public health system (Sistema Único de Saúde), which primarily serves the low-income population. Thus, the results of the PREGNANT substudy will be published as soon as the analyses are completed. The children will be followed from childbirth up to December 2026, which is when the last admitted neonate will turn 5 years old. As the BORN substudy is lengthy, partial results may be disclosed during the course of the study, but the final data set will be made available in the second half of 2026.

Pregnant women included in the study must be aged >18 years. COVID-19 exposure will be defined as a first-time RT-PCR test, serology test, or rapid test that returns positive results during pregnancy and is confirmed by a second test. Nonexposure to COVID-19 will be defined as asymptomatic pregnant women with negative serology tests (immunoglobulin G [IgG] and immunoglobulin M [IgM] tests), which will be conducted at 14-21 days postpartum.

Pregnant women with preexisting chronic diseases (except diabetes and hypertension); those taking continuous medications; those who consume tobacco, alcohol, or other drugs; and those with other suspected or confirmed congenital infections will be excluded.

Neonates whose mothers qualified for inclusion in the PREGNANT substudy (had these women been screened) may also be admitted to the BORN substudy, even if their mothers did not participate in the preceding branch.

Children initially assigned to the control (nonexposed) group who later become infected with SARS-CoV-2 (as confirmed via laboratory tests) during follow-up will be excluded from all analyses (from the time of SARS-CoV-2 infection diagnosis onward). However, they will continue to receive assistance under the same standards until the end of the study.

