### Statistical Analysis

All data will be stored in REDCap (Research Electronic Data Capture; Vanderbilt University), which is a tool for building and managing web-based surveys and databases. All variables will be summarized via standard descriptive techniques according to their type and distribution. For the bivariate analysis, differences in categorical variables between the exposed and unexposed groups will be verified with the Chi-square test or Fisher exact test, whereas differences in continuous variables between the groups will be assessed with the Student *t* test or the Mann-Whitney U test.

For dichotomous outcomes, binomial regression models, which will be adjusted based on the unbalanced and relevant background features of the comparison groups, will be used to estimate the relative risks between the exposed and nonexposed groups. Partial correlation and general linear models will be used to assess the associations between continuous outcome variables and covariates; adjustments for imbalances will be made as appropriate. A *P* value of <.05 will be considered significant. The control group will be composed of nonexposed mother-child dyads that meet the inclusion criteria. However, those with positive serology tests (IgG and IgM tests conducted at 14-21 days postpartum) will not be included in the control group. The groups will not be matched or paired based on age or other variables. However, any differences between the groups will be adjusted later via statistical means.

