The study does have several limitations. Its observational nature limits inferences for causal associations to some extent. However, the cohort study design is the closest observational equivalent to a clinical trial in terms of analytical power, and the objective of the PROUDEST does not ethically allow for interventional experiments because such experiments would imply that pregnant woman will be randomized based on SARS-CoV-2 infection. Moreover, the purpose of the study is to characterize the clinical and pathophysiological phenomena associated with SARS-CoV-2 infection during pregnancy and infancy, not to test the efficacy of any intervention. Thus, we believe that a cohort study is the best possible study design for addressing our objectives. The lack of random allocation for comparison groups will be partially compensated by statistically adjusting for the observed imbalances. Vaccination for SARS-CoV-2 will not be an exclusion criterion because due to the vaccine’s limited accessibility and availability, there are no feasible methods for estimating the proportion of pregnant women that will receive the vaccine. However, the effects of SARS-CoV-2 vaccination can be adjusted and analyzed in small control groups that have either received or not received the vaccine.

The protracted follow-up in the BORN substudy is expected to result in the dropout of several participants. We set a sample size for the study after taking into consideration a 20% loss to follow-up rate. This might ensure that a sizable number of children are available for the final assessment when they reach age of 5 years. However, we cannot avoid survival bias in the long-term data. Nevertheless, given that the continuity of multidisciplinary assistance will be guaranteed for all children in the BORN branch throughout the study period regardless of their withdrawal from the analysis or (temporary) losses to follow-up, we expect that children experiencing health problems associated with in-pregnancy COVID-19 exposure will be less likely to drop out than those who are in perfect health. Therefore, we do expect to have a sufficient number of children in the long run for identifying developmental abnormalities (should they exist), even after some amount of dropout.

Several routine pediatric consultations will be emphasized in the study, such as checking the kind of alimentation that a child is receiving (human milk or formula milk) and promoting the practice of breastfeeding.

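### Serology-only positives count as in-pregnancy exposure without dating the infection, and the postpartum serology rule for controls conflicts with the promised vaccine analysis

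*Protocol article*

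**What the plan says.** All references are to the protocol article.

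- **Exposed group** (Methods, Study Design): "COVID-19 exposure will be defined as a first-time RT-PCR test, serology test, or rapid test that returns positive results during pregnancy", provided that the result "is confirmed by a second test". The type of the second test is not stated.
- **Control group** (same section): "Nonexposure to COVID-19 will be defined as asymptomatic pregnant women with negative serology tests", with IgG and IgM measured at 14-21 days postpartum. The Statistical Analysis section repeats the rule as an exclusion: "those with positive serology tests (IgG and IgM tests conducted at 14-21 days postpartum) will not be included in the control group". Neither place makes an exception for vaccination.
- **Target of the comparison** (Abstract, Methods): group B consists of "control subjects with no laboratory evidence of in-pregnancy exposure to the virus". The contrast of interest is therefore infection during this pregnancy. Aim 8 (Objective) goes further and asks about effects by stage of pregnancy.
- **Vaccination** (Discussion, Study Implications, limitations): "Vaccination for SARS-CoV-2 will not be an exclusion criterion". The same paragraph says that vaccine effects "can be adjusted and analyzed in small control groups that have either received or not received the vaccine".

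**The concern.** A positive antibody test shows that antibodies are present, not when they were acquired. Unless the assay targets something the vaccine does not induce, it also does not show whether infection or vaccination produced them. Requiring a first positive and a confirming test guards against false positive results, but neither dates the infection. A woman infected before conception and first tested in pregnancy satisfies the wording.

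Two things are at stake. First, group A may contain women who were not infected in this pregnancy, which pulls exposed-versus-control contrasts towards no effect and leaves some women without a gestational stage for aim 8. Second, the control rule may remove the very women whom the limitations paragraph relies on for the vaccine analysis. Those who stay would be mainly non-responders or women vaccinated too shortly before the postpartum test, so they are selected on antibody response and do not represent vaccinated controls.

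These are stated group-membership rules, not analysis details. A later analysis plan cannot bring back controls who were never included.

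**Working it through.** The plan gives no figure for contamination, vaccine coverage or seropositivity. The check is therefore first a comparison of its rules, then an illustration under stated assumptions. The plan's one calculated sample size, 195, reproduces to rounding (1.96² × 0.15 × 0.85 / 0.05² = 195.9) and does not bear on this point.

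**1. The rules applied to four women**

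| Woman | Positive serology in pregnancy, confirmed | Positive postpartum serology only |
|---|---|---|
| Infected before conception, first tested in pregnancy | Group A | Not a control |
| Vaccinated, never infected (assay detects vaccine antibodies) | Group A | Not a control |
| Vaccinated, never infected (assay ignores vaccine antibodies) | Does not arise | Does not arise; stays eligible as control |
| Infected in pregnancy, no symptoms, serology only | Group A, stage unknown | Not a control |

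Row 1 does not depend on vaccines at all. Row 2 depends on the assay, whose target the article does not name.

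**2. Dilution of group A**

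Let m be the share of group A not infected in this pregnancy, and assume that these women carry the control risk. Then observed RR = (1 − m) × RR + m.

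- RR 2.0, m = 10%: 0.9 × 2.0 + 0.1 = 1.90.
- RR 2.0, m = 20%: 0.8 × 2.0 + 0.2 = 1.80.

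For power, take 300 per group (Sample Size Calculation), a 5% significance level (Statistical Analysis), an assumed control risk of 10% and an unadjusted comparison:

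| m | True RR 2.0: observed RR, power | True RR 1.8: observed RR, power |
|---|---|---|
| 0 | 2.00, 93% | 1.80, 81% |
| 10% | 1.90, 88% | 1.72, 73% |
| 20% | 1.80, 81% | 1.64, 64% |

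**3. A bound on the vaccine part of group A**

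The Results report 260 infected women included by January 2021, against 300 planned. If those 260 predate vaccination (an assumption), at most 300 − 260 = 40 later entrants could be in group A because of vaccine antibodies: 40/300 = 13.3%. At that limit a true RR of 2.0 becomes 0.867 × 2.0 + 0.133 = 1.87. Pre-conception antibodies have no such bound, because no baseline negative was required from the start of recruitment in July 2020.

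**4. Vaccinated controls left after the postpartum rule**

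Of 300 women screened as controls, with vaccine coverage v and postpartum seropositivity s among the vaccinated (both assumed), those retained number 300 × v × (1 − s):

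| v | Vaccinated | Retained, s = 50% | s = 90% | s = 95% |
|---|---|---|---|---|
| 10% | 30 | 15 | 3 | 1.5 |
| 20% | 60 | 30 | 6 | 3 |
| 40% | 120 | 60 | 12 | 6 |

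The 260 already enrolled do not limit this part. They are exposed women, the article reports no control count, and births run to December 2021.

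**The case against.** The strongest reply is that much of this hangs on details that the article does not give. The assay is not named, and one that ignores vaccine antibodies would remove the vaccine part. The second test might in practice always be RT-PCR. The study calls itself exploratory, and it promises only small vaccinated and unvaccinated control groups. All of this is fair, and it is why the vaccine part is stated conditionally. It does not touch the pre-conception part, and the published wording permits two positive serologies to suffice.

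Several stronger readings are tempting but not supported:

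- *Postpartum serology is the only check on controls.* It is not. Controls must also be asymptomatic, and the Procedures section collects maternal blood at the first prenatal visit and at delivery and lists RT-PCR, IgM and IgG tests. What stands is that the control definition does not use those earlier samples, so an early symptomless infection whose antibodies have faded could pass. This is secondary and unquantified.
- *No serology-only case can be staged.* Symptoms and gestational age are recorded, so symptomatic women can be dated approximately. The gap concerns asymptomatic women.
- *Vaccination becomes inseparable from exposure group.* This does not follow. If most of group A predates vaccination and seropositive vaccinated controls are dropped, both groups are mostly unvaccinated. What is lost is the vaccine analysis among controls.
- *The vaccine analysis is impossible.* Some vaccinated controls may remain. They are few and selected, which makes the analysis unreliable rather than impossible.

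**Conclusion.** The point holds. The exposure definition lets undated serology stand for infection in this pregnancy, so women with pre-conception antibodies can enter group A and asymptomatic serology-only women cannot contribute properly to aim 8. If the assay detects vaccine antibodies, two further consequences follow: some vaccinated, never-infected women can enter group A, and the control rule contradicts the vaccine statement in the limitations.

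The size cannot be derived from the documents. The 10-20% contamination (RR 2.0 observed as 1.9-1.8) is an illustration that assumes the misplaced women carry the control risk. A reader might infer much heavier contamination, but nothing in the article supports a particular share. The 40/300 ceiling on the vaccine part holds only if the first 260 women predate vaccination. The retained-control counts rest on assumed coverage and seropositivity.

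**What to change.** 1. **Split the exposed group.** Call exposure dated if there is a positive RT-PCR or antigen test in pregnancy, or a change from negative to positive between pregnancy samples with no vaccine dose in between. Call the rest undated serology-only. Repeat the main exposed-versus-control comparisons without the undated women. For aim 8, use only infections dated by test, seroconversion or symptom onset.
2. **Record vaccine dates and reconcile the control rule with the limitations paragraph.** There are two options. One is to judge vaccinated women's control status on pre-dose samples, absence of a positive viral test and, where available, an antibody target that the vaccine does not induce, and to exempt them from the postpartum IgG rule. The other is to keep the rule and withdraw the claim that vaccine effects can be analysed among controls.
3. **For unvaccinated controls,** also require the first-prenatal and delivery samples, where available, to be negative.

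The work is mostly redefinition and reclassification from samples that the protocol already collects, and it can be done before analysis, which is scheduled to start after data collection. It has costs. The dated exposed group will be smaller. Women without earlier samples, including exposed mothers of children who entered BORN directly, fall into the undated stratum unless they have a positive viral test in pregnancy. Under the exemption, some undetected infections after vaccination may remain among vaccinated controls.

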### Sample Size Calculation

No precise data are available on the prevalence of SARS-CoV-2 infection among pregnant women in Brazil, but international reports have estimated that up to 15.3% of all pregnancies have been exposed to the virus [38]. Recent data have indicated a birth rate of 44,195 newborns per year in the Federal District [39]. Thus, after considering an “infinite” population (>20,000 pregnant women), assuming a 15% prevalence of SARS-CoV-2–exposed pregnancies, and accounting for a confidence level of 95% and a margin of error of 5%, the minimum sample size for a random sample of SARS-CoV-2–exposed women would be 195. This calculation expectedly yielded a similar number for a random sample of SARS-CoV-2–exposed children. If we set the expected dropout rate for the BORN substudy to 20%, the required number of SARS-CoV-2–exposed mothers (those giving birth to the BORN participants) would increase to 234.

Our sampling approach however is not truly random; it is based on convenience, as eligible subjects will present to the recruitment centers. The aforementioned calculations only serve as a reference for avoiding the overestimation of the inclusion of participants. Given the limited amount of available knowledge regarding the effects of SARS-CoV-2 infection on pregnancy and child development, which resulted in the eminently exploratory character of our study, we adopted an “as much as feasible, but no more than reasonable” approach for defining the sample size.

We set an a priori number of 300 SARS-CoV-2–exposed women for the PREGNANT phase. This will result in the inclusion of the expected 300 SARS-CoV-2–exposed children in the BORN phase. The subject allocation rate between the exposed and control groups was 1:1. This indicated the need for an additional 300 mothers and 300 children to constitute the nonexposed control groups. Hence, the overall sample size of the PROUDEST was set to 1200 participants (600 mother-child dyads consisting of 300 SARS-CoV-2–exposed mother-child dyads and 300 control dyads).

To promote participant retention and completed follow-ups at pregnancy and pediatric outpatient clinics, we will actively search for patients via phone and email.

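### BORN drops control children after a diagnosed postnatal SARS-CoV-2 infection but states no matching rule for exposed children, so later differences cannot be assigned to prenatal exposure alone

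*Protocol article*

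**What the plan says.** The rule stands in the protocol article under Methods, Study Design. It concerns "Children initially assigned to the control (nonexposed) group who later become infected with SARS-CoV-2", with laboratory confirmation required, and says that they "will be excluded from all analyses (from the time of SARS-CoV-2 infection diagnosis onward"). Data from before the diagnosis stay in, so the rule works as censoring. These children go on receiving assistance to the end of the study.

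The same section forms the BORN groups "according to their mothers’ in-pregnancy exposure status". The ninth aim (Objective) is "to evaluate the effects of in-pregnancy COVID-19 exposure on children’s somatic and neurological development and energy metabolism from birth up to 5 years of age".

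No section says what happens to an exposed child infected after birth. Statistical Analysis adjusts for imbalanced background features and does not name postnatal infection. On numbers, Sample Size Calculation says "The subject allocation rate between the exposed and control groups was 1:1", with 300 dyads per group. The limitations text under Discussion says "We set a sample size for the study after taking into consideration a 20% loss to follow-up rate".

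**The concern.** Group membership in BORN is fixed by what happened in pregnancy. A control child infected at age 2 is still a child not exposed in utero, so the exclusion corrects no misclassification. It conditions on an event after baseline, and by the text it does so in one group only.

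The comparison therefore changes as the children age. The exposed group carries prenatal exposure plus whatever postnatal infection does, while the control group is reduced to children with no diagnosed infection. Any effect of childhood infection on growth or neurodevelopment, or of circumstances that go with being infected or tested, enters the contrast as if it came from pregnancy. Covariate adjustment cannot undo this. Once infected controls are out, diagnosed infection occurs in one group only and its effect cannot be estimated across groups.

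Selection may add to this. The article describes no scheduled SARS-CoV-2 testing of children after birth. If testing follows illness or clinic attendance, the controls removed will tend to be the sicker or more closely observed ones.

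**Working it through.** **The plan's own figure.** Sample Size Calculation uses a prevalence of 15%, 95% confidence and a 5% margin: 1.96² × 0.15 × 0.85 / 0.05² = 195.9. The article states 195, which agrees apart from rounding. Its 234 is 195 × 1.20, the 20% allowance for dropout. Neither figure allows for controls excluded after infection, and neither is a power calculation for the group comparison.

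**Inputs from the article.** 300 children per group, and 20% dropout, so 300 × 0.80 = 240 per group; follow-up to age 5; significance level 0.05 (taken as two-sided).

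**Assumed inputs.** The article gives no postnatal infection rate or effect. I take a yearly risk r of confirmed infection of 5%, 10% or 20%, equal in both groups and independent of dropout. Postnatal infection raises an adverse outcome from 10% to 15%, prenatal exposure has no effect, and the remaining controls are all uninfected.

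**Formulas.** Share of controls removed by year t: 1 − (1 − r)^t. Controls left at age 5: 240 × (1 − r)^5. Spurious relative risk: (0.10 + share × 0.05) / 0.10. Difference detectable with 80% power at age 5: 2.80 × √(1/240 + 1/controls left).

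| Confirmed infections per year | 5% | 10% | 20% |
|---|---|---|---|
| Controls removed by 12 months | 5% | 10% | 20% |
| Controls removed by age 5 | 22.6% | 41.0% | 67.2% |
| Controls left of 240 at age 5 | 186 | 142 | 79 |
| Spurious RR at 12 months | 1.025 | 1.05 | 1.10 |
| Spurious RR at age 5 | 1.11 | 1.20 | 1.34 |
| Detectable difference at age 5 (SD) | 0.27 | 0.30 | 0.36 |

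With 240 against 240 the detectable difference is 2.80 × √(2/240) = 0.26 SD.

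**Continuous outcome.** Let q be the cumulative share infected, and suppose postnatal infection shifts a score by −0.3 SD (assumed). The spurious difference is −0.3q, with standard error √(1/240 + 1/(240(1 − q))). Power is for an illustrative true difference of 0.25 SD.

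| q | 10% | 30% | 50% | 70% |
|---|---|---|---|---|
| Spurious difference (SD) | −0.03 | −0.09 | −0.15 | −0.21 |
| Type I error (nominal 5%) | 6% | 15% | 27% | 35% |
| Power, current rule | 76% | 70% | 61% | 46% |
| Power, both groups censored | 74% | 63% | 49% | 32% |
| Power, all children kept | 78% | 78% | 78% | 78% |

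**The case against.** Several points on the other side stand.

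- Retention of infected exposed children is inferred. The article names controls and is silent on the exposed group. It is a condensed text, but its exclusion is stated for one group, and nothing in it extends the rule to the other.
- A reader might infer that the remaining controls are never infected up to age 5. The text does not support that. Removal needs laboratory confirmation and no routine testing of children is described, so these controls are never diagnosed. Undetected infections on both sides would pull the relative risks above toward 1, and 20% confirmed per year is a high case.
- A reader might extend the point to metabolism. Under Procedures, the blood panel at 12 and 24 months is described for exposed children only, so there is no control comparison there for this rule to distort.
- Pre-infection data are kept, so the distortion is small at 12 months and greatest at age 5.
- Loss of controls is the weaker part. A reader might infer that the design loses its planned power, but the article sets no power target and calls the study exploratory. At 5% or 10% per year the detectable difference moves only from 0.26 to 0.27 or 0.30 SD.

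The exploratory aim and the acknowledged limits on causal inference excuse imprecision. They do not excuse a stated rule that makes the groups differ by construction. The limitations text discusses survival bias and dropout, but not this asymmetry.

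**Conclusion.** The concern holds for growth and neurodevelopment in BORN, increasingly with age. As written, the plan censors one group on a post-baseline event and states no counterpart for the other, so a late difference would mix prenatal exposure with postnatal infection. The direction of the problem follows from the text; its size does not. Under the assumed rates and the assumed rise in risk from 10% to 15%, the spurious relative risk runs from about 1.02 to 1.10 at 12 months and from 1.11 to 1.34 at age 5. These figures assume equal infection rates in both groups and no undetected infection among remaining controls. If postnatal infection has little effect on the outcomes, bias by this route is small, and what remains is loss of controls and possible selection through testing.

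**What to change.** Replace the one-sided exclusion with one rule for both groups.

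- **Main analysis:** keep every child in the group set by the mother's exposure in pregnancy, whatever the child's later infection history.
- **Data collection:** state that scheduled study assessments continue and are recorded for infected controls. The article promises them assistance, which need not mean research measurements.
- **Sensitivity analysis:** censor both groups at first confirmed postnatal infection, with inverse-probability-of-censoring weights, or fit infection as a time-varying covariate.
- **Reporting:** give confirmed postnatal infections by group.

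The main change is one of wording. Results says that analysis starts after all data are collected, but Study Design allows partial BORN results to be disclosed earlier, so the rule should be settled before any are produced.

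There are three costs. The main contrast then includes postnatal infection as it naturally occurs. Symmetric censoring has less power than the current rule (for example 63% against 70% at 30% infected), which is why it belongs in a sensitivity analysis. Both the sensitivity analysis and the counts by group rest on infections found by clinically driven testing, which may differ between groups.
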